### Endpoints

The primary endpoint includes changes in the participant’s ability to have penetrative intercourse (without the use of intracavernosal injections, and with or without PDE5i use) from baseline to study completion. This information will be collected using the IIEF-EF questionnaire. The secondary endpoints are sexual activity improvement leading to optimal penetration at follow-ups which will be done according to: (i) Percentage of participants who achieve Minimal Clinically Important Differences (MCID) in IIEF score based on their ED severity at baseline. This is measured using the Change International Index of Erectile Function (IIEF-EF) Questionnaire score; (ii) Change in median International Index of Erectile Function–Erectile Function subdomain (IIEF-EF) from baseline to each follow-up time point in active therapy recipients compared to placebo; (iii) Change in median Sexual Encounter Profile questions number 2 and 3 from baseline to each follow-up time point in active therapy recipients compared to placebo; (iv) Change in median Global Assessment Questionnaire (GAQ) score from baseline to each follow-up time point in active therapy recipients compared to placebo; (v) Change in median Erection Hardness Scale (EHS) score from baseline to each follow-up time point in active therapy recipients compared to placebo; (vi) Changes in duplex ultrasound parameters from baseline to study completion in active therapy recipients compared to placebo.

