### Procedures involved

Upon evaluating the inclusion/exclusion criteria, patients will be recruited to the study and randomized into one of the two groups in a 2:1 ratio (randomization will be performed by a computer software maintained by the Desai Sethi Urology Institute). All participants will be instructed to follow the standard post-RP protocol for ED. Treatments will begin 6 weeks after the RP. The treatment sessions last approximately 20 minutes and are performed in an office environment (see below for session and treatment details). Participants randomized to the treatment group will receive one (1) shockwave session once per week for four (4) weeks, followed by one (1) shockwave session once per month (30 ± 7 days) for the next five (5) months. 1,440 shocks of treatment energy will be applied in every session to each treated region (left and right corpora cavernosa and crura) for a total of 12,960 shocks (Figure 1).

Participants randomized to the sham (control) group will have the same number of sessions, and the machine will be set to deliver 1,440 shock treatments, but a barrier will be placed around the shockwave probe to ensure that no shockwaves are delivered.

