### Follow-up interventions

Follow-up visit will be conducted at 6 months after the last treatment session and shall include: (i) Questionnaires to measure the ability to have penetrative intercourse (IIEF-EF, GAQ, SEP, and EHS); (ii) Recording adverse events; and (iii) Penile Doppler Ultrasound (Table 1).

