## Figures and Tables

**Figure 1: F1:**
[figure not shown]
A) Shockwave therapy being administered; B) Shockwave therapy machine for treatment group; C) Shockwave therapy machine for control/ placebo group.

**Table 1: T1:** The details of the events and procedures participants will undergo throughout the trial.

Schedule of events	Screening	Weekly treatment					Monthly treatment				Follow-up
Visit	Visit 1	Visit 2	Visit 3	Visit 4	Visit 5	Visit 6	Visit 7	Visit 8	Visit 9	Visit 10	Visit 11
Time point	Screening	Week 1	Week 2	Week 3	Week 4	Week 8	Week 12	Week 16	Week 20	Week 24	Month 12
Activity window	0–30 days pre	± 3 days	± 3 days	± 3 days	± 3 days	± 3 days	± 7 days	± 7 days	± 7 days	± 7 days	± 30 days
Informed consent	•										
Medical and urological history	•										
Demographics	•										
Physical examination	•										
Penile Doppler ultrasound	•										•
Blood Test: CBC, HbA1c, PSA and Testosterone	•										
Questionnaires: IIEF-EF, GAQ, SEP, EHS	•	•	•	•	•	•	•	•	•	•	•
Verification of eligibility	•										
Randomization		Group A: Treatment Group B: Sham									
Administration of therapy		•	•	•	•	•	•	•	•	•	
Review concomitant medication		•	•	•	•	•	•	•	•	•	
Review adverse events		•	•	•	•	•	•	•	•	•	•

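### The primary endpoint excludes penetration achieved with intracavernosal injections, but no record of injection use is scheduled at Visit 11 (Month 12), the visit that decides it

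*Protocol article*

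**What the plan says.** **Endpoint.** The Endpoints section makes the primary endpoint the change, between baseline and study completion, in ability to have penetrative intercourse "without the use of intracavernosal injections, and with or without PDE5i use". It then gives the source: "This information will be collected using the IIEF-EF questionnaire". Success therefore has two parts, that penetration occurred and that no injection was used to achieve it. PDE5 inhibitor use is allowed.

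**Deciding visit.** Study completion is Visit 11, at Month 12 in Table 1 and six months after the last session. Follow-up interventions lists its content: "Questionnaires to measure the ability to have penetrative intercourse (IIEF-EF, GAQ, SEP, and EHS); (ii) Recording adverse events; and (iii) Penile Doppler Ultrasound". Medication and injection use are not on the list.

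**Schedule.** In Table 1 the row "Review concomitant medication" is ticked at Visits 2 to 10 and is empty at Screening and at Visit 11. The row below it, "Review adverse events", is ticked at Visits 2 to 11.

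**Background care.** Procedures involved states: "All participants will be instructed to follow the standard post-RP protocol for ED". The Introduction describes the institution's regimen as oral PDE5 inhibitors. It says that roughly 60% to 75% of patients need additional treatment to obtain penetration, and identifies that treatment as injections at the time of intercourse.

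**The concern.** The no-injection condition separates this endpoint from penetration by any means. The Discussion gives the trial's purpose as lowering the proportion of men who need more invasive treatment in order to penetrate. To apply the condition, the trial must know each man's injection use over the period that his Month 12 questionnaire covers.

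The article schedules no record of it. If the schedule is followed as printed, a man who penetrates at Month 12 only because he injects can return the same questionnaire answers as a man who does not need injections, and both would count as successes. Such misclassification raises the success rate in both arms. If equally common among true failures in each arm, it shrinks the difference between arms, because the sham arm has more true failures to convert. The estimate would be diluted and would answer a different question. Injection use that was not asked about at Month 12 cannot be reliably recovered later.

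**Working it through.** **1. Is the blank cell real?** Table 1 has eleven visit columns. The adverse-event row has ten ticks (Visits 2 to 11) and the medication row has nine (Visits 2 to 10). The Visit 11 column therefore survives in the text, and the blank in the medication row is not a conversion fault. The Follow-up interventions list independently gives the same Visit 11 content without medication.

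**2. Does anything else supply injection status at Visit 11?** The Endpoints section names the IIEF-EF. Follow-up interventions adds the GAQ, SEP and EHS as measures of the same ability. None of the four is said to record injections, and no diary or injection log is mentioned. The last scheduled medication review is Visit 10 (Week 24), about six months before Month 12.

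**3. The plan's own sample size.** Inputs from Sample size calculation: 20% control, 40% active, 80% power, 5% significance, 63 control and 126 active. Two-sided, pooled variance, two active per control, no continuity correction:

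- pooled rate = (0.20 + 2 × 0.40)/3 = 0.333
- n(control) = [1.960 × √(0.333 × 0.667 × 1.5) + 0.842 × √(0.20 × 0.80 + 0.40 × 0.60/2)]² / 0.20² = [1.960 × 0.5774 + 0.842 × 0.5292]² / 0.04 = 62.2, rounded up to 63
- total = 63 + 126 = 189, as stated

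Power at 63/126 is 80.6% by the normal approximation. It is 78.8% with the two-sided Fisher exact test that Data analysis names for success rates.

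**4. Illustration of the consequence.** Assumption, not in the document: a share u of true failures, equal in both arms, penetrates with injections and is scored a success.

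- control rate = 0.20 + 0.80u
- active rate = 0.40 + 0.60u
- difference = 0.20 × (1 − u)

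Exact two-sided Fisher power at 63/126, by full enumeration:

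| u | Control | Active | Difference (points) | Power |
|---|---|---|---|---|
| 0 | 20.0% | 40.0% | 20.0 | 79% |
| 2% | 21.6% | 41.2% | 19.6 | 75% |
| 5% | 24.0% | 43.0% | 19.0 | 71% |
| 10% | 28.0% | 46.0% | 18.0 | 64% |
| 20% | 36.0% | 52.0% | 16.0 | 53% |
| 30% | 44.0% | 58.0% | 14.0 | 43% |

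Equal u need not hold. If true failures in the sham arm used injections more often, say 20% against 10% (also assumed), the rates would be 36% and 46% and power about 23%.

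**The case against.** The strongest reply is that this is a condensed article. Questionnaire instructions and case report form fields commonly sit in the full protocol, and men may be told to answer the IIEF-EF for attempts without injections. The article does not reproduce the questionnaire, so nothing in it shows that the instrument cannot carry the condition. This stands against one stronger reading, that success cannot be classified at all. The supportable statement is that it cannot be classified from the data the article schedules. The reply does not remove the point. The article names the source, lists the visit content and prints a schedule with medication review at nine visits and not at the deciding one.

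A reader might also infer that baseline injection use goes unrecorded, because the medication row is blank at Screening and Materials and Methods names past PDE5 inhibitor use. The document does not support that. Table 1 ticks medical and urological history at Screening, which could capture injections, and reviews medication at Visit 2 (Week 1). At baseline the item is only not named explicitly.

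A reader might take the 60% to 75% in the Introduction as the share of men injecting at Month 12. It describes need for additional treatment, not uptake and not use at that visit. It makes injection use plausible in both arms but fixes no value of u, and at small u the loss of power is modest.

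Finally, Follow-up interventions names four questionnaires, so the IIEF-EF is the sole instrument only in the primary-endpoint text. None of the four is said to record injections, so the gap remains.

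**Conclusion.** The point holds for Visit 11. The primary endpoint carries a no-injection condition, and two places in the article agree on a Month 12 visit that does not collect the information needed to apply it. Because this concerns the primary endpoint and is cheap to correct, it should be put right before the first Month 12 visit.

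The stated sample size of 189 is unaffected as arithmetic. The possible loss is in the meaning of the endpoint and in power: from 79% to between 75% and 43% for u from 2% to 30%, with the difference falling from 20 to between 19.6 and 14 points. These figures rest on an assumed u, equal in both arms, and on no injection record being taken at Month 12 outside the printed schedule. They show sensitivity and do not forecast the result.

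**What to change.** - **Table 1 and Follow-up interventions:** tick concomitant-medication review at Visit 11 and add it to the list of visit content.
- **Visit 11 form:** record intracavernosal injection and PDE5 inhibitor use over the IIEF-EF recall period.
- **Screening:** name injection use explicitly in the medical and urological history, so that baseline is recorded in the same way.
- **Endpoints:** state that success requires both the IIEF-EF penetration response and penetration achieved without injections in that period. The section currently gives no IIEF-EF item or cut-off, so the sponsor must name them. Replace the sentence that gives the IIEF-EF as the source with one that also names the injection record.

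These changes concern data capture and classification only and leave clinical care as it is. The cost is a minor amendment and one short form at existing visits.

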**Results::**

Statistical analysis, encompassing ANOVA for continuous variables and Fisher’s exact test for categorical ones, will evaluate demographic characteristics, baseline data, and primary as well as secondary outcomes for statistical significance. Detailed analysis of trends, subgroup comparisons, and treatment effects will provide a comprehensive understanding of the impact of SWT on post-RP ED.

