### Data analysis

The average and standard deviation of all relevant variables, including demographic and baseline characteristics, primary and secondary outcomes will be calculated. IIEF-EF and EHS scores will be analyzed using ANOVA with repeated measures throughout the study, in order to compare the trends between the treatment and sham group. GAQ, SEP and success rates will be analyzed and compared between the groups according to Fisher’s exact test in each of the endpoints. The statistical significance will be set at P<0.05.

Demographic characteristics such as age and ED duration will be compared between treatment group and sham group using student’s T-Test. Other demographic characteristics, such as medical background and risk factors will be compared between these groups using Fisher’s Exact Test.

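### Ultrasound, IIEF-EF and EHS are assigned ANOVA with no baseline covariate; adjusting for the screening value already collected would gain precision at almost no cost

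*Protocol article*

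**What the plan says.** - **Endpoint form.** In Endpoints, secondary endpoint (vi) is "Changes in duplex ultrasound parameters from baseline to study completion in active therapy recipients compared to placebo". Table 1 marks penile Doppler ultrasound at Screening and Month 12 only, so each man contributes one pair of values per parameter.
- **General method.** The abstract's Results paragraph describes "Statistical analysis, encompassing ANOVA for continuous variables and Fisher’s exact test for categorical ones".
- **IIEF-EF and EHS.** Data analysis states: "IIEF-EF and EHS scores will be analyzed using ANOVA with repeated measures throughout the study, in order to compare the trends". Table 1 collects both at every visit, including Screening. Endpoints (ii) and (v) are worded as "Change in median International Index of Erectile Function–Erectile Function subdomain (IIEF-EF) from baseline to each follow-up time point" and "Change in median Erection Hardness Scale (EHS) score from baseline to each follow-up time point".
- **GAQ and SEP.** Data analysis sends these, with success rates, to Fisher's exact test: "GAQ, SEP and success rates will be analyzed and compared between the groups according to Fisher’s exact test in each of the endpoints".
- **Not stated.** Data analysis names no test for ultrasound. Nowhere does the article mention adjustment for the screening value, and nowhere does it exclude it.

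**The concern.** If ultrasound is compared as raw change by ANOVA, the analysis fixes the weight on the screening value at exactly one, whatever the data show. That is efficient only when a one-unit difference at screening predicts about a one-unit difference at Month 12. Here the first scan comes some weeks after prostatectomy and the second about a year later. In between lies recovery that is likely to vary in a population mixing nerve-sparing and non-nerve-sparing surgery. A modest correlation is therefore plausible, although the article gives no value. With equal SDs and a correlation below 0.5, a change score is noisier than ignoring the screening value altogether.

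For IIEF-EF and EHS, a repeated-measures ANOVA with no baseline covariate may likewise leave information in the screening score unused.

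What is at stake is the precision of secondary comparisons. Ultrasound matters somewhat more than the others because it is the only efficacy measure that is not a questionnaire, and the Discussion concedes difficulties with blinding.

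**Working it through.** **Inputs from the article.** 63 sham and 126 active men; 5% significance and 80% power (Sample size calculation); ultrasound at two times (Table 1).

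**Inputs that must be assumed.** The correlation r between screening and Month 12, and the two SDs. The article gives neither.

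**1. The article's own figure.** The 189 was derived for the binary primary endpoint (20% v 40%). With a pooled-variance, two-sided test and twice as many active as sham men, the average rate is (0.2 + 2×0.4)/3 = 0.333. The sham arm needs

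[1.960×√(1.5×0.2222) + 0.842×√(0.16 + 0.24/2)]² / 0.2² = (1.132 + 0.445)² / 0.04 ≈ 62.2, so 63.

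The total is 3×63 = 189, which reproduces. No continuous endpoint enters this calculation, so nothing below alters it.

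**2. Variance with equal SDs** (in units of SD², per man):

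- change score: 2(1−r)
- Month 12 value alone: 1
- ANCOVA: 1−r²
- ratio of ANCOVA to change score: (1+r)/2

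| Assumed r | Change | ANCOVA | ANCOVA/change | Extra men for change score, 2/(1+r)−1 |
|---|---|---|---|---|
| 0.3 | 1.40 | 0.91 | 0.65 | 54% |
| 0.5 | 1.00 | 0.75 | 0.75 | 33% |
| 0.7 | 0.60 | 0.51 | 0.85 | 18% |
| 0.9 | 0.20 | 0.19 | 0.95 | 5% |

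The change-score variance exceeds 1, that of the Month 12 value alone, whenever r is below 0.5.

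**3. The same in power.** Take a difference that ANCOVA detects with 80% power. The change score has power Φ(2.802×√((1+r)/2) − 1.960):

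- r = 0.3: Φ(0.299) = 62%
- r = 0.5: Φ(0.466) = 68%
- r = 0.7: Φ(0.623) = 73%

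The 80% anchor is only a yardstick; the trial was not sized for ultrasound.

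**4. Unequal SDs.** With screening SD s0 and Month 12 SD s1, the change-score variance minus the ANCOVA variance is

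(s0² + s1² − 2r·s0·s1) − s1²(1−r²) = (s0 − r·s1)².

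This is never negative, so apart from the degree of freedom spent, adjustment cannot lose. It can, however, gain very little. For an illustrative s0 = 4 and s1 = 9:

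- r = 0.2: 82.60 v 77.76, change-score power 78%
- r = 0.3: 75.40 v 73.71, change-score power 79%
- r = 0.5: 61.00 v 60.75, change-score power 80%

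**5. Chance baseline difference.** Its standard error is √(1/63 + 1/126) = 0.154 SD. This is ordinary sampling variation, already inside the standard error of an unadjusted comparison. ANCOVA removes the part that the screening value explains.

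**The case against.** **The article does not say the ultrasound comparison is unadjusted.** Endpoint (vi) defines an outcome, not a model. Regressing change on arm and screening value gives exactly the same arm effect as regressing the Month 12 value on arm and screening value. Data analysis names no test for ultrasound, so ANOVA rests on one general sentence in the abstract. Covariates are often left to an analysis plan, which is not shown here. This stands as a limit on the claim. What remains is that the article does state an analysis method, and that method carries no baseline covariate.

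**A reader might infer that IIEF-EF and EHS are also compared as raw change scores, with the same percentage losses.** The article does not support that. It assigns repeated-measures ANOVA to scores, in order to compare trends. It does not say that Screening is one of the repeated times, though the endpoint wording and Table 1 make this a natural reading. It also specifies no Month 12 versus Screening contrast. The two-time-point formulas do not describe a trend test over 11 visits, so the figures above apply to ultrasound only.

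**A reader might extend the point to all the continuous or questionnaire endpoints.** GAQ and SEP go to Fisher's exact test and are outside it. Nor is ANOVA the only method named for any continuous variable: Student's t-test is given for age and ED duration, but those are baseline descriptions, not outcomes.

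**A reader might infer bias from baseline imbalance.** Under randomisation the change-score comparison is unbiased with valid type I error. The loss is in precision alone.

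**The size is assumed.** That is correct. At r = 0.9, or with a much smaller spread at screening, little is lost.

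**Adjustment does not resolve everything here.** Endpoints (ii) and (v) are worded as changes in medians, whereas ANOVA and ANCOVA compare means. That mismatch is separate and remains.

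**Conclusion.** The point holds as a free improvement to secondary analyses. The article defines ultrasound as change from baseline and gives ANOVA without a baseline covariate as its method for continuous outcomes. It gives IIEF-EF and EHS a repeated-measures ANOVA, again with no baseline covariate. Adjusting for the screening value is a better method than the one stated.

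For ultrasound, if it is analysed as raw change and the SDs are equal, the variance is 1/0.65, 1/0.75 or 1/0.85 times that of ANCOVA at r = 0.3, 0.5 or 0.7. The excess falls to about 5% at r = 0.9 and can be close to zero when the screening SD is much the smaller. These correlations and SDs are assumptions. For IIEF-EF and EHS the direction of the advice is the same, but no size can be given. The primary endpoint and the sample size of 189 are unaffected.

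**What to change.** In Data analysis, add wording to this effect:

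- Each ultrasound parameter at Month 12 will be compared between arms by ANCOVA with its screening value as covariate.
- For IIEF-EF and EHS, the post-baseline scores will be modelled as the repeated outcomes, with the screening score as a covariate rather than as one of those outcomes. The adjusted arm difference at Month 12 will be reported with a 95% CI.

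If an unseen analysis plan already specifies this, the article and the plan need only be brought into line.

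The cost is one or two sentences and one degree of freedom per model. All the values are already scheduled in Table 1, so no visits, measurements or patients are added.

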### Procedures involved

Upon evaluating the inclusion/exclusion criteria, patients will be recruited to the study and randomized into one of the two groups in a 2:1 ratio (randomization will be performed by a computer software maintained by the Desai Sethi Urology Institute). All participants will be instructed to follow the standard post-RP protocol for ED. Treatments will begin 6 weeks after the RP. The treatment sessions last approximately 20 minutes and are performed in an office environment (see below for session and treatment details). Participants randomized to the treatment group will receive one (1) shockwave session once per week for four (4) weeks, followed by one (1) shockwave session once per month (30 ± 7 days) for the next five (5) months. 1,440 shocks of treatment energy will be applied in every session to each treated region (left and right corpora cavernosa and crura) for a total of 12,960 shocks (Figure 1).

Participants randomized to the sham (control) group will have the same number of sessions, and the machine will be set to deliver 1,440 shock treatments, but a barrier will be placed around the shockwave probe to ensure that no shockwaves are delivered.

### Follow-up interventions

Follow-up visit will be conducted at 6 months after the last treatment session and shall include: (i) Questionnaires to measure the ability to have penetrative intercourse (IIEF-EF, GAQ, SEP, and EHS); (ii) Recording adverse events; and (iii) Penile Doppler Ultrasound (Table 1).

### Safety

Any adverse event (penile hematoma or penile fracture) and eventual complication must be recorded at any time during the treatments and the follow up visits, and throughout the entire study duration. Patients will be instructed to alert the study investigator by telephone of any side effects occurring in the period after the treatment and until the study ends. The investigators will conduct continuous reviews of the data and subject safety, keeping track of the number of subjects, significant toxicities in accordance with the protocol and observed responses, which will be discussed at research committee meetings. All grade 3–5 adverse events (CTCAE v4.0), regardless of association with the SWT, will be entered into study database and reviewed at research committee meetings. In addition, all adverse reactions considered “serious” will be entered into the research database and reviewed by the Surgeon monitor on an ongoing basis.

